#### Oxygen saturation, heart rate, and cerebral perfusion pressure

The data from the 3 outcomes will be recorded from the Philips IntelliVue with the time chart as exposed in Fig. 1.

**Fig. 1 Fig1:**
[figure not shown]
SPIRIT (Standard Protocol Items: Recommendations for Interventional Trials) table of enrollment, intervention, and assessments. *Recommended content can be displayed using various schematic formats. See SPIRIT 2013 Explanation and Elaboration for examples from protocols. **List specific timepoints in this row

#### Expiratory and Inspiratory peak flow

Data will be collected in 30 s periods at T−60 m, T−5 m, at the beginning and every minute, T+ 5 m, and T+ 30 m; all expiratory peak flows will be checked and the best will be recorded from every 30 s sequence. Maquet Servo U and I, Hamilton C5 ventilators will be used.

#### Applied pressure

In order to assure that the technique is performed consistently, the chest compression pressure made by the Physiotherapist will be monitored and data recorded during the procedure application time. The Tekscan ComfortMat 1 will be the device used to measure and record the pressure values (g/cm^2^).

#### Blood O_2_ and CO_2_

Recent studies identify a tight control in the lower limits of blood CO_2_ partial pressure as a protective factor in case of brain injury, because high CO_2_ levels induce arterial vasodilatation as shown in laboratory studies. We will perform arterial blood gas 5 min prior to and at the end of the technique application.

#### CT scan

We will use the images acquired and interpretation made by Radiologists to identify the type and location of the injury.

### Participant timeline {13}

The participant timeline is shown in Fig. 1.

### Sample size {14}

To obtain the sample size needed for this study we worked with the software Ene 3.0 and based the estimations on the changes in intracranial pressure with the techniques performed in the study by Thiesen et al. (2005), in which the mean of baseline measures (equivalent to the control group) was 6.9 mmHg, mean in the experimental group was 7.2 mmHg 30 mins post-physiotherapy and joint standard deviation was 2.0 mmHg in patients with ICP 0–10 mm and the mean of baseline measures (equivalent to the control group) was 13.7 mmHg, mean in the experimental group was 12.7 mmHg 30 mins post-physiotherapy and joint standard deviation was 2.5 mmHg in patients with ICP 10–20 mmHg.

With a power of 80% and to detect that the difference of means is equal to the equivalence limit by means of a *T*-Student test for two independent samples, assuming that the equivalence limit is 2.0 mmHg and a level of confidence of 95%, we obtained a sample size of 25 patients in each group: control and experimental. The total number is 50 subjects for this RCT.

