### Eligibility criteria {10}

#### Inclusion criteria:

Intubated patients with mechanical ventilation in Volume Controlled, Pressure Controlled and Volume Controlled Pressure Regulated modes during the 48 h prior to the application of the techniqueSevere head injury with a GCS≤8 before sedation or after the surgical procedures, when needed.Hemodynamic stability (MAP> 65 mmHg)Respiratory stability (PEEP <10cmH_2_O and FiO_2_ < 60%)Intracranial Pressure Stability (0 <ICP < 20 mmHg)RASS sedation scale of − 5 pointsInformed consent obtained

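### The 80% power at 25 per group fits a difference test with one ICP band's SD; it is not established for equivalence or for the whole 0–20 mmHg population

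*Protocol article*

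**What the plan says.** Protocol article, Sample size {14}: the calculation rests on a cited 2005 study that reports two ICP bands separately. In the 0–10 mmHg band the means are 6.9 at baseline and 7.2 at 30 minutes, with SD 2.0. In the 10–20 mmHg band they are 13.7 and 12.7, and the "joint standard deviation was 2.5 mmHg in patients with ICP 10–20 mmHg". The text goes on "With a power of 80" per cent, "to detect that the difference of means is equal to the equivalence limit", using a two-sample t test, "assuming that the equivalence limit is 2.0 mmHg" and "a level of confidence of 95" per cent. The result: "we obtained a sample size of 25 patients in each group: control and experimental". It does not say which band, SD or true difference was entered, or whether the test is one- or two-sided.

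Elsewhere in the article:

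- Objectives {7}: the null hypothesis is no change in ICP and the alternative is a change.
- Eligibility criteria {10}: one range covers both bands, "Intracranial Pressure Stability (0 <ICP < 20 mmHg".
- Statistical methods {20a}: the hypothesis is tested with an independent-samples t test or a Mann-Whitney test. Whether the outcome is the ICP level or its change is not fixed. The regression takes ICP differences as a dependent variable, and baseline ICP is not among its listed covariates.
- Outcomes {12}: ICP is recorded 60, 30 and 5 minutes before the intervention and at its start.

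**The concern.** Two things do not fit together.

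First, a true difference equal to the limit is the alternative of a difference test. In an equivalence test it is the edge of the null hypothesis, where equivalence should be declared only rarely. The sample-size sentence therefore uses equivalence vocabulary for what reads as a difference calculation, and the hypotheses and tests elsewhere are those of a difference test.

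Second, SDs of 2.0 and 2.5 describe patients within a 10 mmHg band. The trial mixes both bands, whose means lie 6.8 mmHg apart at baseline and 5.5 mmHg apart at 30 minutes. An SD for the whole range of ICP levels must include that gap.

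The article's discussion says that the aim is to learn whether the technique is safe. If 25 per group is taken as 80% power for equivalence, a non-significant t test could be read as evidence of safety that the design may not be able to provide.

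**Working it through.** **Inputs** (Sample size {14}): limit or difference 2.0 mmHg; SD 2.0 (0–10 band) and 2.5 (10–20 band); band differences 7.2 − 6.9 = +0.3 and 12.7 − 13.7 = −1.0; power 80%; confidence 95%; 25 per group. The SDs are read as SDs of ICP levels, because they are printed beside mean levels.

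**1. Reproducing 25.** Two-sided 5% difference test, SD 2.5:

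n = 2 × (1.96 + 0.8416)² × (2.5/2.0)² = 24.5, rounded up to 25. Exact t-test power at 25 is 79.1%.

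Two other routes also return 25:

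- One-sided non-inferiority, margin 2.0, SD 2.5, no true difference, alpha 0.025.
- Two one-sided tests (TOST) with the 0–10 band inputs: limit 2.0, SD 2.0, true difference 0.3, alpha 0.025 per side. Power is 81.6% at 25 and 79.6% at 24.

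Each route uses the SD of one band only.

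**2. Equivalence power at 25 per group** (t-based TOST, limit ±2.0; numerical integration, with selected cells confirmed by simulation):

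| SD | True difference | 90% CI (0.05 per side) | 95% CI (0.025 per side) |
|---|---|---|---|
| 2.0 | +0.3 | 90% | 82% |
| 2.5 | 0 | 75% | 58% |
| 2.5 | −1.0 | 40% | 27% |

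For 80% power the second row needs 28 or 34 per group, and the third row 78 or 100.

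**3. Unadjusted ICP levels, whole 0–20 mmHg range.** The article does not give the share w of patients in the lower band, so it is assumed.

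Pooled variance = w × 2.0² + (1 − w) × 2.5² + w(1 − w) × (gap in means)²

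- Baseline means, w = 0.5: 2 + 3.125 + 0.25 × 6.8² = 16.685, SD 4.08. Power for 2.0 mmHg is 40%.
- 30-minute means, w = 0.5: 5.125 + 0.25 × 5.5² = 12.69, SD 3.56. Power is 49%.
- Mixes from 20:80 to 80:20, either set of means: SD about 3.0 to 4.1, difference-test power 40% to 62%.

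**4. Change scores.** Assume SD 4.08 at both times and within-patient correlation ρ, which the article does not give. Then SD of change = 4.08 × √(2(1 − ρ)).

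| ρ | SD of change | Power for 2.0 mmHg |
|---|---|---|
| 0.5 | 4.08 | 40% |
| 0.7 | 3.16 | 59% |
| 0.8 | 2.58 | 77% |
| 0.85 | 2.24 | 87% |

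**5. Comparison adjusted for baseline ICP.** Residual SD = 4.08 × √(1 − ρ²). At ρ = 0.5, 0.7 and 0.8 this is 3.54, 2.92 and 2.45, with difference-test power of about 50%, 66% and 81%. These figures ignore the one degree of freedom used by the covariate.

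**The case against.** The other side has three good arguments.

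- **The calculation may really be an equivalence one.** The article calls 2.0 mmHg an equivalence limit, and the 0–10 band inputs give exactly 25 under TOST at 0.025 per side. This stands: a reader might infer that 25 can only be a difference-test figure, but the article does not say which inputs were used, so that cannot be established. The rescue is partial, however. It covers only the lower band, and the upper band's own inputs would need 100 per group under the same rule.
- **The equivalence shortfall can be small.** With SD 2.5, no true difference and the usual 90% interval, power is 75% and 28 per group would suffice. That is correct. The larger shortfall (58%) requires reading the stated 95% confidence as a 95% interval, and sidedness is not given.
- **The loss from mixing bands may not occur.** A reader might infer that the trial simply has about 40% power. The documents do not support that, because the primary test is not tied to ICP levels. The sample-size text speaks of changes, the hypotheses are about change, and the regression uses differences. On change scores much of the gap between bands cancels. This stands, but 80% is then reached only with a within-patient correlation slightly above 0.81 (at SD 4.08), and the article gives neither that correlation nor an SD stated to be for change.

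**Conclusion.** The power statement is wrong as written. The 25 per group most plausibly gives 79% power for a two-sided difference of 2.0 mmHg with SD 2.5, in agreement with the hypotheses and test but not with the equivalence label. With the 10–20 band SD, equivalence power is 75% or 58% at zero true difference, and 40% or 27% at that band's own difference of −1.0.

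For the 0–20 mmHg population actually enrolled, the 80% is unsupported rather than disproved. It fails (40–62%) if unadjusted levels are compared, over band mixes of 20:80 to 80:20. On change scores it runs from about 40% to 87% for correlations of 0.5 to 0.85. These ranges assume that the printed SDs are SDs of levels and, for change scores, an equal SD of 4.08 at both times.

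It would also go too far to treat 2.5 as the residual SD after baseline adjustment. It is a within-band SD, and the residual SD depends on the missing correlation.

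**What to change.** Keep 50 patients and make four changes:

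1. In Sample size {14}, state whether the aim is to detect a difference or to show equivalence, and bring Objectives {7} and Statistical methods {20a} into line with that choice. If equivalence is chosen, state the confidence level of the interval compared with the limit.
2. Make the primary comparison the between-arm difference in ICP adjusted for pre-intervention ICP, which Outcomes {12} already records.
3. Restate power for that test with an SD for the whole 0–20 mmHg range. Show it over a range of assumed within-patient correlations, since no single value can be defended from the article.
4. Do not describe 25 per group as giving 80% power for equivalence.

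The cost is redrafting of three sections and a stated power that looks less favourable. No extra patients or measurements are needed.

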### Recruitment {15}

The participants included in this study will be selected from the admitted patients with severe acute brain injury, ICP monitoring, and IMV in the ICU of the Hospital Álvaro Cunqueiro, Galicia, Spain. The number of patients that we had at our ICU with severe acute brain injury in 2019 was about 80. The selected patients must meet the following inclusion criteria: patients intubated with mechanical ventilation in controlled volume mode, controlled pressure and controlled volume controlled by pressure during the 48 h prior to the application of the technique; hemodynamic stability (MAP> 65 mmHg); respiratory stability (PEEP <10cmH_2_O and FiO_2_ < 60%); stability of intracranial pressure (0 <ICP < 20 mmHg); RASS sedation scale of 5 points; and informed consent obtained (Annex 1). Patients meeting any of the exclusion criteria will not be enrolled: thoracic fractures: costal, sternal, clavicular, scapular or unstable vertebral; abdominal injuries that prevent the application of local manual compression; systemic or local changes that occur with abdominal volume increase; and fractures or conditions in the lower right limb that contraindicate the performance of passive mobilization of the 1st metatarsophalangeal joint.

## Assignment of interventions: allocation

### Sequence generation {16a}

The allocation sequence was generated at the GraphPad QuickCalcs page (https://www.graphpad.com/quickcalcs/randomize2/) with no repetition and 50 subjects with allocation in 2 groups.

### Implementation {16c}

The allocation sequence generated as described in 16a will be applied after the acceptance and informed consent signing. Once accepted to be part of the study, the PI will enroll and assign the subjects according to the sequence generated at GraphPad.

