**Methods:**

Randomized clinical trial, double-blinded. Patients with acute brain injury on invasive mechanical ventilation > 48 h will be included and randomized in two groups. In the control group, a technique of passive hallux mobilization will be applied, and in the intervention group, it will be performed using the rapid chest compression technique. Intracranial pressure (main variable) will be collected with an intracranial pressure monitoring system placed at the lateral ventricles (Integra Camino).

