### Trial design {8}

Randomized controlled trial, double-blinded with a control group and intervention group.

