## Assignment of interventions: blinding

### Who will be blinded {17a}

*Patients* will be blinded, as they are sedated.

*Data analysts* will be blinded as the data package will be given at the end of the data collection with no reference to the main variable.

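### The principal investigator enrols and assigns from a pre-generated list with no concealment safeguard described, a replacement's arm is known in advance, and the double-blinded label and analyst blinding are misdescribed

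*Protocol article*

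**What the plan says.** **Allocation.** Sequence generation {16a} describes a single list made with an online tool, "with no repetition and 50 subjects with allocation in 2 groups". Implementation {16c} says that the sequence "will be applied after the acceptance and informed consent signing" and that "the PI will enroll and assign the subjects according to the sequence generated at GraphPad".

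**Other duties of the same person.** Under Intervention description {11a}, the principal investigator shares safety monitoring, including ICP, with the clinical team. Under Data management {19}, the principal investigator keeps and anonymises the data.

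**Replacement.** Procedure for unblinding if needed {17b} removes any unblinded subject from the database and enrols another into the same arm.

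**Blinding.** Trial design {8} reads "Randomized controlled trial, double-blinded with a control group and intervention group". Who will be blinded {17a} names two parties. Patients "will be blinded, as they are sedated". Data analysts are blinded because "the data package will be given at the end of the data collection with no reference to the main variable". The Methods part of the Abstract defines that variable: "Intracranial pressure (main variable) will be collected".

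**Analysis.** Statistical methods {20a} plans a Student t test or a Mann-Whitney test. It also plans a regression whose covariates include the type of technique and the pressure applied. The Applied pressure section shows that this pressure is the chest-compression pressure, so it exists in the intervention arm only.

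**The concern.** Randomisation protects the comparison only if the person who decides whether and when a patient enters cannot foresee the arm. Here one person enrols and assigns from a list that already exists, and nothing in the text separates the two acts. There is room to choose: eligibility spans ICP from above 0 to below 20 mmHg, and the technique is applied at a single moment that someone must pick. There is also a likely direction, because the Discussion records the team's belief that the technique is safe when adequately applied. Steadier patients, or steadier moments, could drift towards chest compression without any intent. That would favour a conclusion of safety, and no analysis can repair it afterwards.

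The blinding text adds a second problem. Readers give weight to a double-blind label, yet nobody who selects, treats or observes patients is listed as blinded. The one safeguard that could still work, a blinded analyst, is described in a way that cannot be carried out.

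**Working it through.** **1. The statements side by side**

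| Item | What the article fixes | Consequence |
|---|---|---|
| Enrol and assign | One person does both, from a list of 50 made in advance | No described barrier between the list and the enrolment decision |
| Timing | Sequence applied after consent | Limits use of the list, but does not stop the enroller knowing the next arm |
| Replacement | Same arm as the erased subject | Arm certain before that patient is chosen |
| Blinded parties | Sedated patients; data analysts | Bedside team and enroller not listed |
| Analyst package | No reference to the main variable | The main variable is ICP, without which the primary test cannot be run |
| Covariates | Applied pressure, chest compression only | Values in one coded group only would identify that group |

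**2. The plan's own sample size, for scale.** Inputs from Sample size {14}: difference 2.0 mmHg, SD 2.5 mmHg, 95% confidence, 80% power.

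n = 2 × [SD × (z₀.₉₇₅ + z₀.₈₀) / difference]² = 2 × [2.5 × (1.960 + 0.842) / 2.0]² = 24.5, rounded up to 25 per group.

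The stated 25 is reproduced, and this point does not change it.

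**3. How predictable the list could be.** For a concealed random list with exactly 25 per arm, the best strategy is always to guess the arm used less often so far. Expected correct guesses = 25 + ½ × [4²⁵ / C(50,25) − 1] = 25 + ½ × (8.91 − 1) = about 29 of 50. If the enroller could see the list, the figure would be 50 of 50. The article does not say which applies.

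**4. What a given bias would do to the primary test.** Let b be an assumed selection bias in mean ICP, on whatever measure is compared. The standard error is SD × √(2/25), which is 0.707 at SD 2.5 and 0.566 at SD 2.0 (the two SDs in {14}). The non-centrality is b / SE. With no true effect, the probability that a two-sided 5% t test on 48 degrees of freedom rejects is:

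| b (mmHg, assumed) | SD 2.5: b/SE | SD 2.5: type I error | SD 2.0: b/SE | SD 2.0: type I error |
|---|---|---|---|---|
| 0.25 | 0.354 | 6.4% | 0.442 | 7.2% |
| 0.50 | 0.707 | 10.7% | 0.884 | 13.9% |
| 1.00 | 1.414 | 28.3% | 1.768 | 41.0% |

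**5. The same bias acting towards safety.** If the true rise were 2.0 mmHg and selection hid 1.0 mmHg of it, the expected difference would be 2.0 − 1.0 = 1.0 mmHg. From the table, the chance of detecting it at SD 2.5 is 28.3%, against the planned 80%.

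**6. Is 1 mmHg conceivable?** The two baseline strata in {14} have means of 6.9 and 13.7 mmHg, 6.8 mmHg apart. Shifting 4 of 25 patients between strata moves an arm's mean by 4/25 × 6.8 = 1.1 mmHg. This applies to raw ICP levels only. Raw levels pooled over both strata would have an SD above 2.5, so this step must not be combined with the percentages in step 4. If ICP change is compared, a shift in starting level largely cancels, and what remains is the choice of steadier patients or moments.

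**The case against.** Several stronger readings are tempting, and the documents do not support them.

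- **That the principal investigator holds the list.** No section says who generated it or who keeps it. Assigning according to a sequence would also fit sealed envelopes or release by a third party.
- **That allocation is unconcealed and all 50 assignments are foreseeable.** The article has no concealment item (16b), and a fuller protocol may contain one. The text supports only that no safeguard is described in a procedure that gives both acts to one person.
- **That the principal investigator may stop treatment at discretion.** Sections {11a} and {11b} tie stopping to the listed limits or to the clinical team's judgement. The principal investigator shares monitoring and is given no such discretion.
- **That the double-blind claim is simply false.** Two blinded parties are named, so the label misleads about who is blinded but is not flatly contradicted. A bedside team cannot be masked to chest compression versus toe mobilisation.

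Other points against also carry weight. ICP is read from a continuous monitoring device at set times, which limits assessor bias. Most eligibility criteria are numeric, which narrows the room for steering. The main-variable wording may be a slip for the group variable. Nothing says that the applied-pressure data reach the analyst before the primary test.

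These points narrow the concern but do not remove it. Device readings do not prevent selection of patient or moment. A concealment paragraph elsewhere would not cure the same-arm replacement rule. The analyst wording, slip or not, cannot be followed as it stands.

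**Conclusion.** The point holds in this form: the article gives enrolment and assignment to one person who also monitors ICP and keeps the data, it describes no concealment safeguard, and it makes any replacement's arm known beforehand. The double-blinded label needs qualifying, and the analyst blinding needs rewriting.

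The size of any bias is unknown. The figures of about 6% to 28% rest on three assumptions: a bias of 0.25 to 1.0 mmHg in the compared measure, SD 2.5 mmHg, and an unadjusted two-sided t test with 25 per group. They show sensitivity and do not predict what will happen. The change should be made because it is cheap before recruitment and cannot be made good later.

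**What to change.** 1. **Custody and release.** Have the list held by someone outside enrolment and bedside work, such as existing research unit staff, or placed in sequentially numbered, opaque, sealed envelopes. Release each arm only after consent, the eligibility check and the ICP reading 5 min before the technique.
2. **Replacement.** Withdraw the rule of erasing a subject and refilling the same arm. Keep every randomised subject in the analysis. At the least, give any replacement the next concealed allocation.
3. **Label.** Describe the trial as patient- and analyst-blinded with an unblinded bedside team, in the Abstract and in Trial design {8}.
4. **Analyst package.** Supply ICP with arms coded A and B. Withhold applied-pressure data until the primary analysis is locked, and run the regression that needs them afterwards.

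The cost is one set of envelopes or a little time from existing staff, plus a few lines of text and an amendment notice. No extra patients or measurements are needed. If the full protocol already has a concealment procedure, the first item reduces to stating it in {16c}.

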## Assignment of interventions: blinding

### Who will be blinded {17a}

*Patients* will be blinded, as they are sedated.

*Data analysts* will be blinded as the data package will be given at the end of the data collection with no reference to the main variable.

### Procedure for unblinding if needed {17b}

The need of unblinding is not permissible and if for any circumstantial reason it happens, the subject will be erased from the database and not included in this study. Another subject will be enrolled in the same group of allocation.

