### Intervention description {11a}

Intervention group: the application of the technique will be carried out in a single moment and will be applied with the patient in supine decubitus with 30° elevation of head and trunk, the rapid chest compression technique will be applied once in the expiratory time of each 3 respiratory cycles during 5 min by a physiotherapist. Safety monitoring of heart rate, blood pressure, intracranial pressure, peripheral oxygen saturation, and cerebral perfusion pressure will be performed by the clinical team and the principal investigator. The intervention will stop if reached some of the safety values presented below or when the clinical team considers.

Control group: the technique will be performed in a single moment and will be applied with the patient in supine decubitus with 30° elevation of head and trunk. The passive mobilization technique of the right first metatarsophalangeal joint will be applied to the available range of flexion-extension, performing 15 repetitions per minute and for 5 min by a physiotherapist. Safety monitoring of heart rate, blood pressure, intracranial pressure, peripheral oxygen saturation, and cerebral perfusion pressure will be performed by the clinical team and the principal investigator. The intervention will stop if reached some of the safety values presented below or when the clinical team considers.

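### The rule that erases any unblinded patient and refills the same arm is a post-randomisation exclusion with non-random replacement, on a poorly defined trigger and with no provision to keep safety data

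*Protocol article*

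**What the plan says.** All references are to the protocol article.

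- **Procedure for unblinding if needed {17b}** declares unblinding not permissible and then fixes what follows if it happens for any reason: "the subject will be erased from the database and not included in this study. Another subject will be enrolled in the same group of allocation".
- **Sequence generation {16a}** describes a fixed list, "with no repetition and 50 subjects with allocation in 2 groups". **Implementation {16c}** says that the sequence "will be applied after the acceptance and informed consent signing" and that "the PI will enroll and assign the subjects according to the sequence generated at GraphPad".
- **Who will be blinded {17a}** names two parties: patients, who "will be blinded, as they are sedated", and the data analysts, who receive the data once collection has ended.
- **Intervention description {11a}** says of safety monitoring, in both arms, that it "will be performed by the clinical team and the principal investigator".
- The **Abstract** (Discussion) gives the aim as finding out whether the technique is safe. **Sample size {14}** sets an equivalence limit of 2.0 mmHg with 25 patients per arm.

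**The concern.** A randomised patient is removed because of something that happened after randomisation, and the successor's arm is set by rule rather than by chance. Four things follow from the text alone.

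1. The patients analysed are no longer the patients randomised.
2. For each replacement, the person who enrols knows the arm before choosing whom to approach, however well the list itself is concealed.
3. Nothing says that the erased patient's safety data are kept. An analysis plan, seen or unseen, cannot recover erased records.
4. The protocol does not define which event counts as unblinding or who declares it. The PI assigns the arm and, with the clinical team, monitors the patient during the procedure. A rule built on breaking the blind fits poorly where those at the bedside have none to break, and so leaves room for discretion.

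If erasure were related to the intracranial pressure (ICP) response, the estimated effect would be biased. If the largest rises under compression were the ones erased, the bias would run towards finding no harm.

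**Working it through.** **Inputs.** From Sample size {14}: limit 2.0 mmHg, 25 per arm, 80% power, 95% confidence, SD 2.5 mmHg (ICP 10–20 mmHg) or 2.0 mmHg (ICP 0–10 mmHg). The number erased, k, is an assumption, because the protocol gives no unblinding rate. A second assumption is that these SDs, reported beside mean ICP levels, also describe ICP changes.

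**Step 1: the plan's own figure.** n per arm = 2 × SD² × (1.960 + 0.842)² / 2.0². With SD 2.5 this is 2 × 6.25 × 7.849 / 4 = 24.5, so 25. The stated size is reproduced with SD 2.5, which is therefore used below.

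**Step 2: worst-case shift in one arm's mean.** Suppose the k largest of 25 values are erased and each is replaced by a fresh patient from the same population. The expected fall in the mean is SD × S(k) / 25, where S(k) is the sum of the k largest expected standard normal order statistics for n = 25. The five largest are 1.965, 1.524, 1.263, 1.067 and 0.905.

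- k = 3: S = 4.752; 2.5 × 4.752 / 25 = 0.48 mmHg; 0.48 / 2.0 = 24% of the limit.
- k = 5: S = 6.724; 2.5 × 6.724 / 25 = 0.67 mmHg; 0.67 / 2.0 = 34% of the limit.
- With SD 2.0 the same cases give 2.0 × 4.752 / 25 = 0.38 and 2.0 × 6.724 / 25 = 0.54 mmHg.

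Replacement matters. Dropping the patients without refilling would divide by 22 or 20 and give 0.54 or 0.84 mmHg, but that is not the rule as written.

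**Step 3: effect on the comparison.** Simulation of 40,000 trials, 25 per arm, SD 2.5, with the k largest changes erased and replaced in the compression arm only. *Rejection* is the two-sided 5% t test. *False equivalence* is a 90% confidence interval lying wholly within ±2.0 mmHg when the true difference is 2.0. The interval rule is an assumption made here, because the protocol names a limit but no equivalence test.

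| k | Mean estimate, true difference 2.0 | Rejection (power) | False equivalence | Rejection, true difference 0 |
|---|---|---|---|---|
| 0 | 2.00 | 79% | 4.8% | 4.9% |
| 1 | 1.80 | 73% | 9.4% | 6.4% |
| 2 | 1.65 | 67% | 13.8% | 8.8% |
| 3 | 1.52 | 61% | 18.5% | 12.3% |
| 5 | 1.33 | 52% | 27.2% | 18.3% |

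**Step 4: the other end of the range.** If the erased patients are chosen without regard to outcome, the mean estimate stays at 2.00 to 2.01 mmHg and power at about 79% for every k from 1 to 5.

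**The case against.** The strongest reply is that the rule would rarely be used and has no stated link to harm. Patients are deeply sedated and analysts see data only at the end, so reaching a safety limit unblinds neither. The treating staff already know the technique. Under Criteria for discontinuing or modifying allocated interventions {11b}, stopping is not tied to unblinding or to erasure. This stands.

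A reader might infer that the rule will mainly delete compression patients who were harmed, and that their safety stops would vanish from the report. The documents do not support that. The unblinding rule makes no distinction between arms, monitoring and stopping are worded alike for both, and no section makes a safety event an unblinding event.

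Two further points have weight. Erasing 3 or 5 of 25 means 12% or 20% unblinding in one arm, a rate with no source in the protocol. And the PI already enrols and assigns from the list, so concealment in general is a separate question that changing this rule would not settle.

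What the reply does not answer is that erasure and same-arm refilling after randomisation are written into the protocol without limit by reason, timing or outcome. Nothing ensures that erasure is unrelated to outcome, and an erased record leaves no means of checking.

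**Conclusion.** The point holds as a defect in a stated rule. The loss of the as-randomised comparison, the non-random assignment of replacements and the missing provision for safety data follow from the text and do not depend on any link with outcome.

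Bias in the ICP estimate is conditional on such a link. The shift in the arm mean runs from about 0 to a worst case of about 0.48 mmHg (k = 3) or 0.67 mmHg (k = 5), that is 24% or 34% of the 2.0 mmHg limit. This assumes SD 2.5 mmHg, normally distributed changes, replacement as the rule requires, and erasure of exactly the largest rises in one arm. These figures bound the harm for the assumed k; they are not an expected bias.

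**What to change.** Replace the paragraph under {17b} with the following provisions.

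- Every randomised patient stays in the database and is analysed in the arm assigned, with all safety data.
- Each unblinding is logged with its time and reason and is reported.
- A sensitivity analysis leaves those patients out.
- If a replacement is ever needed, for example when consent is withdrawn before the procedure, the new patient takes the next position of a random list, not a chosen arm. The present list has exactly 50 positions, so spare positions must be generated in advance.

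The cost is one paragraph, a longer list and notification of the ethics committee. The planned 25 per arm does not change.
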